#### 3.4.3. Food Frequency Questionnaire

Dietary patterns are assessed using a semiquantitative 137-item food frequency questionnaire (FFQ) previously validated in Spain [149]. The questionnaire is based on the most common portion sizes (weight (g) and volume (mL)) and food groups in the Spanish population that are multiplied by the consumption frequency for each food. Frequency categories included never or almost never; 1–3 times a month; 1, 2−4 or 5−6 times a week and 1, 2−3, 4−6, >6 times a day. Although the FFQ indicates a range of consumption for each food, in the present study, the exact frequency of consumption is specified (2 times a week, 3 times a week, etc.). The information collected from the FFQ is obtained face-to-face with the patient by a trained nutritionist. The FFQ assesses the individual’s diet through nine food categories and 150 items: milk and milk products; eggs, meat and fish; vegetables and vegetables; fruit; legumes, cereals and potatoes; oils and fats; pastries and pastries; sauces, fried foods, snacks, sugars and salt; and drinks. It also includes a special category about dietary supplement/product consumption.

#### 3.4.4. Physical Activity

To assess physical activity patterns, the short version of the International Physical Activity Questionnaire (IPAQ) validated in the Spanish population is used [78]. This questionnaire consists of seven questions that explore physical activity patterns over the past 7 days. The questionnaire is divided into two sections. In the first section, patients are asked to describe the type, frequency, and intensity of activities performed in four areas (at work, at home, during transportation, and during leisure time). Questions are presented on a frequency scale (days per week) and duration (minutes per day). In the second section, patients are asked to indicate the time spent sitting during a typical day of the week. Questions are presented on a time scale (hours per day). Once the questionnaire is completed, a total physical activity score is calculated based on the duration and frequency of reported activities. The results provide quantitative [total energy metabolism rate (MET) per minute/week] and qualitative (low, moderate, or vigorous activity) information on physical activity.

To calculate the quantitative physical activity, time dedicated to each activity is taken into account (8 MET for vigorous activities, 4 MET for moderate activities, and 3.3 MET for walking) by applying the following equation: Total MET (minutes/week) = MET × minutes/day × days/week.

To obtain qualitative information on physical activity, the following assumptions are considered. Low Activity (no activity is recorded or some activity is reported but not enough to fall into moderate activity), Moderate Activity (≥3 days of vigorous activity at least 20 min/day or ≥5 days of moderate activity and/or walking at least 30 min/day or ≥5 days of any combination of walking, moderate or vigorous activity or ≥ 600 total MET min/week), Vigorous Activity (≥3 days/week of high activity and at least ≥1500 MET min/week or ≥7 days/week of any combination of walking, moderate or vigorous activity + ≥3000 MET min/week). Time sitting (h) or walking (min) is also recorded.

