#### 2.8.6. Physical Activity

Resting energy expenditure is increased in many cancer patients; however, total energy expenditure appears to be lower because of a reduction in daily physical activity [74]. In cancer patients, total energy expenditure may be estimated from standard formulas for resting energy expenditure and standard values for physical activity level [75]. To calculate the total energy expenditure and energy requirements, physical activity is evaluated. Maintenance or an increase in the physical activity level to maintain physical function, muscle mass, and metabolic pattern is a clinical practical recommendation in cancer patients [43]. Increased physical activity reduces the risk and improves survival of patients in several cancers [76].

To calculate the energy balance, the energy intake obtained in the 72 h daily food record is to be compared with the total energy expenditure calculated from the Institute of Medicine, Food and Nutrition Board [77], plus the energy derived from physical activity obtained through the International Physical Activity Questionnaire [78]. Physical activity will be evaluated at the beginning (v0) and at the end of the intervention (v5). The mean of the difference between intake and food frequency found between these visits will be statistically compared with those found in the rest of the treatments. The evolution of diet will also be evaluated through the different intervention visits where it will be measured (v1, v3, v4, and v5).

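### The moderate-activity rule joins its last two conditions with *or* where they belong together, so five very short walks a week count as moderate; the physical-activity section also names a diet quantity as what is compared (minor)

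*Protocol article*

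**What the plan says.** Section 3.4.4 uses the short IPAQ and derives a quantitative result (weekly MET-minutes) and a qualitative one (low, moderate or vigorous).

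- Weights: "8 MET for vigorous activities, 4 MET for moderate activities, and 3.3 MET for walking".
- Score: "Total MET (minutes/week) = MET × minutes/day × days/week".
- Moderate, first alternative: "≥3 days of vigorous activity at least 20 min/day".
- Moderate, second alternative: "≥5 days of moderate activity and/or walking at least 30 min/day".
- Moderate, third and fourth alternatives: at least five "days of any combination of walking, moderate or vigorous activity or" a weekly total of at least 600 MET-min.
- Vigorous: either at least three days of high activity and at least 1500 MET-min/week, or at least seven "days/week of any combination of walking, moderate or vigorous activity" plus at least 3000 MET-min/week.
- Low: no activity, or too little to reach moderate. It is the residual class.

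Section 2.8.6 lists physical activity among the secondary outcomes. Its comparison sentence reads "The mean of the difference between intake and food frequency found between these visits" and says that this is compared between treatments. The next sentence concerns the evolution of diet.

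**The concern.** As written, the moderate class has four separate entry routes. The third sets a number of days with no minimum minutes and no MET total. The fourth sets a MET total with no minimum number of days. A patient who takes a few minutes' walk on five days, and a patient who is active on one long day, are both placed above low.

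The activity category is the stated qualitative result of a listed secondary outcome. Because low is whatever is left over, an over-wide moderate class takes patients directly from it. That blurs the distinction between low and moderate, and makes the category less able to register a change within a patient or a difference between arms.

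Section 2.8.6 adds a separate problem. In the section on physical activity, the quantity named for comparison is dietary, so the reader is not told whether MET-minutes, the category or both will be compared.

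**Working it through.** The plan states no figure to reproduce. The check applies the Section 3.4.4 rule to example weeks, once as written (*or*) and once with the last two conditions joined (*and*).

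**Inputs (all Section 3.4.4).** Vigorous 8, moderate 4, walking 3.3 MET; weekly score = MET × minutes/day × days/week.

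**Step 1: example weeks.**

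| Week | MET-min/week | As written | Joined |
|---|---|---|---|
| Walk 5 min × 5 days | 3.3×5×5 = 82.5 | moderate | low |
| Walk 10 min × 5 days | 3.3×10×5 = 165 | moderate | low |
| Walk 20 min × 5 days | 3.3×20×5 = 330 | moderate | low |
| Walk 30 min × 5 days | 3.3×30×5 = 495 | moderate | moderate (second alternative) |
| Vigorous 20 min × 3 days | 8×20×3 = 480 | moderate | moderate (first alternative) |
| Vigorous 75 min × 1 day | 8×75×1 = 600 | moderate | low |
| Walk 30 min × 4 days | 3.3×30×4 = 396 | low | low |
| Walk 60 min × 3 days | 3.3×60×3 = 594 | low | low |
| Walk 60 min × 1 day | 3.3×60×1 = 198 | low | low |

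To reach 600 MET-min in one day takes 600/8 = 75 min of vigorous activity, 600/4 = 150 min of moderate activity, or 600/3.3 ≈ 182 min of walking.

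**Step 2: redundancy.** Anyone with five or more days of moderate activity or walking of 30 minutes each also has five or more days of some combination of activities. Under *or*, every week that meets the second alternative already meets the third, so the 30-minute floor can never change a classification. It has a function only if the five-day combination carries a volume condition of its own.

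**Step 3: parallel structure.** The vigorous class pairs days with a MET total twice: three days with 1500, and seven days of any combination with 3000. Only the moderate class separates the pair.

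**Step 4: does low survive under *or*?** Yes. It keeps everyone with fewer than five active days and under 600 MET-min who does not meet the three-day vigorous rule. Two invented grids illustrate this; every cell has equal weight and neither is patient data.

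- Walking only, 0–7 days by 10–60 min in steps of 10: low is 28 of 48 cells under *or* and 36 of 48 under *and*.
- Mixed: 0–7 walking days, 0–3 moderate days and 0–2 vigorous days, with a common duration of 10, 20, 30, 45 or 60 min and days added across activity types. Low is 107 of 480 under *or* and 249 of 480 under *and*.

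The direction is certain, because any week that is low under *or* is also low under *and*. The size depends entirely on the assumed grid.

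**Step 5: Section 2.8.6 beside Section 2.8.5.** The diet section uses the same comparison of intake and food frequency, followed by the same sentence on the evolution of diet. Both recur in the physical-activity section, where neither names an IPAQ quantity.

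**The case against.** The strongest reply is that the consequence is small. Section 2.8.6 measures activity in order to estimate energy expenditure and energy balance, which is a quantitative use, and the continuous score does not depend on the category rule. No sentence sets out a between-arm test of the category specifically, and the primary outcome is electrogustometry. This stands, and it is why the point is minor.

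A reader might infer that the low class almost vanishes, that nearly every ambulatory patient becomes moderate, or that the category can no longer show change. The documents do not support this. They give no activity distribution, and ordinary weeks such as four 30-minute walks stay low. A reader might also infer that the baseline description overstates activity, but Table 3 has no activity row. Nor does any single active day suffice: it must reach 600 MET-min. Finally, 600 is not the floor of the moderate class, since the first two alternatives admit 480 and 495 under either reading. A shortfall should not be expressed as a share of 600.

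It can also be said that the article paraphrases a validated questionnaire and condenses a fuller protocol, so the actual derivation may be correct. That is possible, and the text cannot show that any patient was misclassified. But the rule as printed is what an analyst would program, and it conflicts with its own neighbouring clauses.

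On Section 2.8.6, the general statement in Section 2.8 already has changes from v0 to v5 compared between groups, so the intended quantity can be guessed. The specific sentence still names something else.

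**Conclusion.** Wrong as written, and minor. The last two moderate conditions are printed as alternatives although the redundancy of the 30-minute clause and the form of the vigorous class both indicate that they belong together. Weeks as light as 82.5 MET-min are classed as moderate, as is any week reaching 600 MET-min whatever the number of days. The residual low class is too small, by an amount that the documents do not allow anyone to estimate.

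This conclusion rests on the wording and MET weights of Section 3.4.4 alone. The affected result is the category; total MET-min/week and the primary outcome are untouched. The diet wording in Section 2.8.6 is a separate drafting error and adds no weight to the classification point.

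**What to change.** In Section 3.4.4, replace the third and fourth alternatives with one criterion: activity of any mix of walking, moderate and vigorous on at least five days, **and** a weekly total of at least 600 MET-min. Keep the first two alternatives unchanged. Derive the category at each visit from the recorded days and minutes, and re-derive it wherever the literal *or* was applied.

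In Section 2.8.6, replace the references to intake, food frequency and the evolution of diet with the change in total MET-min/week and in IPAQ category, compared between treatments.

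The cost is one joined condition, two sentences and, if needed, a re-run of one derived variable. No new data are required.

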#### 3.4.5. Quality of Life

Quality of life (QoL) is evaluated using the EORTC QLQ-C30 questionnaire for cancer patients validated in Spanish [150]. The questionnaire consists of 30 questions referring to the previous week. This is formed by 5 functional scales (daily activities and physical, emotional, cognitive, and social functioning), 3 symptomatic scales (fatigue, pain, nausea, and vomiting), 1 overall health scale, and 6 questions about dyspnea, insomnia, anorexia, constipation, diarrhea and economic impact. Values between 1 and 4 points are assigned (absolute (1 point), little (2 points), quite (3 points), and a lot (4 points)). The last two items (29 and 30) are given a score from 1 to 7, with 1 being terrible and 7 being excellent.

Scores obtained are standardized from 0 to 100 points to determine the disease impact for each scale. To score the scales, first, the average of the items that contribute to the scales (raw score, *RS*) is estimated. *RS* = (*Q*_1_ + *Q*_2_ +…+ *Q*_n_)/*n*. Then, a linear transformation is used to standardize the RS using the following formulas: Functional scales = [1 − (RS − 1)/range)] × 100, Symptom scales/items and global health status (QoL) = [(R − 1)/range] × 100. The range is the difference between the maximum possible value of *RS* and the minimum possible value. A high score on the global health status and functional scales indicates a better quality of life, while a low score on the symptoms scale indicates a decrease in quality of life.

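### Section 3.4.5 reads a low QLQ-C30 symptom score as worse quality of life, but under its own scoring formula a low score means fewer symptoms

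*Protocol article*

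**What the plan says.** Section 3.4.5 (Quality of Life) sets out how the EORTC QLQ-C30 is scored and read.

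- **Response coding, 1 to 4:** "Values between 1 and 4 points are assigned (absolute (1 point), little (2 points), quite (3 points), and a lot (4 points".
- **Global health items:** "The last two items (29 and 30) are given a score from 1 to 7, with 1 being terrible and 7 being excellent".
- **Functional scales, with reversal:** "Functional scales = [1 − (RS − 1)/range)] × 100".
- **Symptom scales, single items and global health, without reversal:** "Symptom scales/items and global health status (QoL) = [(R − 1)/range] × 100".
- **Range:** "The range is the difference between the maximum possible value of *RS* and the minimum possible value".
- **Reading of the result:** high is better for the global and functional scales, "while a low score on the symptoms scale indicates a decrease in quality of life".

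Section 2.8.7 makes quality of life a secondary outcome. The mean change from v1 to v5 is compared between treatments, and its course is followed over v1, v3, v4 and v5. No other section gives a direction for the symptom scores.

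**The concern.** The scoring formula and the reading rule stand a few lines apart and point in opposite directions for symptoms. The formula makes the score rise with symptom burden, while the reading rule treats the low end as the bad end.

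The direction of benefit on a patient-reported secondary outcome is at stake. Section 3.4.5 lists fatigue, pain, and nausea and vomiting as symptom scales. The single questions that share the formula include anorexia, constipation and diarrhea. Several of these bear directly on the food-intake rationale, and Section 6 expects quality of life to improve. A reader who applies the sentence would report symptom relief in an arm as deterioration, and worsening as benefit.

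Two features of the data handling give the written rule more weight. Section 2.12 replaces variable names with alphanumeric codes to mask the analysis and sends the file to a separate university department. Section 2.11 opens the treatment codes only after the statistical analysis is complete. Analysts who may not see meaningful variable names have more reason to lean on what the protocol says about direction.

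**Working it through.** All inputs come from Section 3.4.5.

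**Ranges.** Items scored 1 to 4: 4 − 1 = 3. Items scored 1 to 7: 7 − 1 = 6.

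**Step 1: the two directions that the text states correctly.**

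Functional = [1 − (RS − 1)/3] × 100. Global = [(RS − 1)/6] × 100.

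| Scale | Raw mean (RS) | Score |
|---|---|---|
| Functional | 1 | 100 |
| Functional | 2 | 66.7 |
| Functional | 3 | 33.3 |
| Functional | 4 | 0 |
| Global | 1 (worst) | 0 |
| Global | 4 | 50 |
| Global | 7 (best) | 100 |

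High is better for both, as stated.

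**Step 2: the symptom scales.**

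Symptom = [(RS − 1)/3] × 100.

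| Raw mean (RS) | Calculation | Score |
|---|---|---|
| 1 | (1 − 1)/3 × 100 | 0 |
| 2 | (2 − 1)/3 × 100 | 33.3 |
| 3 | (3 − 1)/3 × 100 | 66.7 |
| 4 | (4 − 1)/3 × 100 | 100 |

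The strongest response scores 100, so a low score means fewer symptoms. The stated reading does not reproduce.

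**Step 3: could a different coding rescue the sentence?** The printed label for 1 point is unclear and is probably a translation of the none category. The result does not depend on it, because the labels for 2, 3 and 4 already rise in order. Suppose nevertheless that 1 were the worst answer. The symptom reading would then be true, but the functional formula would give 100 to the worst patients, and the first half of the same sentence would be false. One formula reverses and the other does not, so no single 1-to-4 coding makes both halves true.

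**Step 4: how many scores are touched.** Section 3.4.5 lists 5 functional scales + 3 symptom scales + 1 global scale + 6 single questions = 15 scores. The sentence names the symptom scales, which is 3. The formula is headed "Symptom scales/items and global health status (QoL"), so carrying the reading over to the single items gives 3 + 6 = 9 of 15.

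**Illustration.** A fatigue mean falling from 3 to 2 moves the scale from 66.7 to 33.3, a change of −33.3. The number is computed correctly and is an improvement. The sentence would call it a decrease in quality of life.

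**The case against.** The contradiction itself cannot be argued away. The strongest case on the other side concerns its consequences, and most of that case stands.

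- **No score is wrong.** A reader might infer that 9 of 15 scores carry the wrong sign. They do not. Coding, averaging and transformation are coherent apart from the R/RS slip, and they give correctly directed numbers.
- **The tests do not use the sentence.** Section 2.8.7 compares mean changes, and Section 2.13 provides for two-sided tests at p < 0.05. Estimates and p-values are the same whether or not the sentence is corrected. No responder definition, composite or sample size in the article rests on it.
- **The reach is narrower than 9 if read literally.** The sentence names the symptom scales, while the six single questions, one of them on economic impact, are listed separately. Extension to them is plausible because they share the formula, but it is not stated.
- **Misreporting is not certain.** An analyst who knows the instrument, or who reads the formula just above, may notice. The other two directions in the same sentence are right, which suggests a drafting slip.
- **There is a partial cross-check.** Sections 2.8.8 and 3.4.7 grade nausea, vomiting, constipation and diarrhea separately by CTCAE, where the direction is clear, so a reversed reading would conflict visibly with those data. There is no such check for fatigue, pain, dyspnea, insomnia or anorexia.

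These points limit the harm. They do not make the sentence right, and it is a stated rule rather than a detail left to an analysis plan.

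**Conclusion.** The sentence is wrong as written and should be fixed. By the protocol's own formula a high symptom score means more symptoms, and the text reads the scale the other way round. The reversed interpretation covers 3 symptom scales, and up to 9 of 15 scores if it is extended to the single items.

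The fault is one of interpretation only. The documents do not support the stronger conclusion that the quality-of-life analysis is numerically wrong, or that symptom relief will necessarily be reported as harm; that would happen only if someone followed the sentence against the formula. The primary outcome and the sample size are untouched, and quality of life is one of many secondary outcomes in an exploratory pilot, so this does not rank with faults that undermine the main analysis.

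The conclusion assumes only that the printed response order (2 below 3 below 4) and the printed formulas are those the trial uses.

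**What to change.** 1. Replace the closing sentence of Section 3.4.5 with: *A high score on the functional and global health scales indicates better quality of life; a high score on the symptom scales/items indicates more symptoms (worse).* Naming the items as well as the scales also settles the 3-or-9 question.
2. Label the direction of benefit for each scale in the results tables, and carry the same label into the coded database described in Section 2.12.
3. Change R to RS in the symptom and global formula, to match the defined symbol.

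The cost is one sentence, one symbol and table labels. No data need be recollected, rescored or reanalysed. The change should be made before the quality-of-life results are interpreted.

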#### 3.4.6. Miraculin-Based Food Supplement Perception Efficacy

A visual–analog scale (VAS) was designed by the researchers to obtain information about the miraculin-based food supplement consumption patient perception efficacy. The questionnaire includes 5 questions to answer on a 10 cm scale, where 0 means not at all or very bad and 10 means very good or very effective. The questions included are as follows: Do you notice a food taste change after consuming the product? Does food taste better to you? Does it allow you to eat more food? What is your opinion about the product? Are you satisfied with the effectiveness of the product? Does the administration of the product seem adequate to you?

#### 3.4.7. Tolerance and Adverse Events

A diary sheet is given where the patient writes down the possible adverse events, symptoms presented, symptoms date (beginning and end), intensity (mild, moderate, intense), a possible relationship with the product (yes, no, it is possible) and behavior adopted. On every visit, the patient is also asked about any other discomforts not written down because they are considered light and related to product consumption. Gastrointestinal disorders such as abdominal distension, abdominal pain, nausea, regurgitation or gastroesophageal reflux, vomiting, constipation, diarrhea, and flatulence are defined and recorded based on Common Terminology Criteria for Adverse Events (CTCAE) from the National Cancer Institute [82]. These adverse events are classified as Grade 0 (not described), Grade 1 (mild), Grade 2 (moderate), Grade 3 (severe), Grade 4 (mortality risk), and Grade 5 (death associated with an event).

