### 2.2. Ethics and Dissemination

The final protocol was approved by the Scientific Research and Ethics Committee of the University Hospital La Paz. The research protocol in version 1 was approved in June 2022 (HULP Code 6164) in compliance with The Ethical Standards of the Declaration of Helsinki about the recommendations guiding physicians in biomedical research involving human subjects. All researchers are to know and follow the ICH Harmonized Tripartite Guidelines for Good Clinical Practice.

Before signing the informed consent form, all subjects will be informed by a study researcher about the study characteristics (verbally and in writing) and what their inclusion in the clinical trial means (File S2). Patients will be informed that they can decide at any time to abandon their participation in the study, notifying their doctor without having to give any reason and without detriment to their usual medical treatment. In this case, they will be asked if their decision is related to any adverse event due to the consumption of the miraculin-based tablets.

All study data will be processed by members of the research team in a database specifically created for this study and dissociated from any data that could identify the patient. The processing of personal data will follow the Spanish Organic Law (Ley Orgánica) 3/2018, of 5 December, and the General Data Protection Regulation of the European Union (EU) 2016/679 of 27 April 2016.

Only the study investigators will have access to the patient’s data with prior authorization from the principal investigator. Once the study is completed, all the data collected in paper format will be archived in the external archive store of HULP and will be kept for the period established by local legislation.

Once the clinical trial has finished, following the provisions of the Spanish Legislation (Real Decreto 1090/2015), the researchers and the promoter will publish the obtained results (positives or negatives). Publication will take place in a publicly accessible scientific journal.

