#### 2.8.8. Tolerance and Adverse Events

Nausea, diarrhea, dysphagia, vomiting, constipation, and abdominal pain are gastrointestinal symptoms that are used to measure product consumption tolerance. However, they are also considered supportive indicators that can impair food intake or absorption, an etiological criterion used for malnutrition diagnosis [23]. Symptoms of intensity, frequency, and duration will be collected in a diary sheet throughout the study and evaluated at every visit, and the percentage change between visits will be compared between treatments. Gastrointestinal disorders will be judged using Common Terminology Criteria for Adverse Events (CTCAE) from the National Cancer Institute [82]. These adverse events will be used to discern the severity of food intake or absorption impairment and evaluate tolerance to the nutritional intervention. CTCAE will be evaluated at the beginning (v1) and end of the intervention (v5), and the percentage change between these two visits will be compared between treatments. Evolution will also be measured on v1, v3, v4, and v5.

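### The supplementary visit question on tolerance is limited to light discomforts related to the product, so on that one route presumed causality decides what is collected and could differ by arm

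*Protocol article*

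**What the plan says.** Section 3.4.7 describes three routes.

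- **Diary.** The patient writes down possible adverse events with dates, intensity (mild is the lowest level) and "a possible relationship with the product (yes, no, it is possible"). Relatedness is an attribute of an event already recorded, and an event judged unrelated stays in the data.
- **Visit question.** At each visit the patient is also "asked about any other discomforts not written down because they are considered light and related to product consumption".
- **CTCAE.** Gastrointestinal disorders "are defined and recorded based on Common Terminology Criteria for Adverse Events (CTCAE") and graded from 0 to 5, with no condition on cause.

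Section 2.8.8 adds that symptoms "will be collected in a diary sheet throughout the study and evaluated at every visit", and that "the percentage change between visits will be compared between treatments". It places CTCAE assessment at visits 1, 3, 4 and 5.

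**The concern.** Comparing symptoms between randomised arms is straightforward when every arm is asked the same thing and the answer does not depend on what the patient believes caused the symptom. The supplementary question departs from this. Its purpose is to recover what the diary missed, yet as worded it recovers only items already judged to be product-related.

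Two things could follow. A mild effect of the product that is put down to chemotherapy would not be recovered in any arm. And if the tendency to blame the product differs by arm, the recovered symptoms would differ by arm even when the true rates are equal.

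The second is a realistic possibility in this trial. Miraculin turns sour into sweet (section 1). Participants are encouraged to eat acidic foods (section 2.5). The perception scale asks them directly whether they notice a taste change (section 3.4.6). Blinding is described through the presentation and identical characteristics of the product (section 2.11), which does not hide its effect in the mouth. From visit 2 on, visits follow an infusion by days, when toxicity is greater (section 4.2), so a mild symptom often has two plausible causes.

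**Working it through.** There is no figure in the plan to reproduce. The check is to set the routes side by side and then illustrate the mechanism.

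**Step 1: which routes depend on presumed cause?**

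| Route | Where | Condition on cause |
|---|---|---|
| Diary | 3.4.7, 2.8.8 | None; relationship recorded as yes, no or possible |
| CTCAE grading of gastrointestinal disorders | 3.4.7, 2.8.8 | None stated |
| QLQ-C30 symptom items | 2.8.7, 3.4.5 | None |
| Supplementary visit question | 3.4.7 | Light and related to the product |

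Only the last route is filtered.

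**Step 2: which symptoms can the filter affect?** Those that are mild, absent from the diary, and not picked up by CTCAE grading or the QLQ-C30. Nausea, vomiting, diarrhea, constipation and abdominal pain have an unfiltered route at visits 1, 3, 4 and 5. What is left is mild symptoms outside those lists, and mild symptoms around visit 2, when neither CTCAE grading nor the QLQ-C30 is scheduled.

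**Step 3: illustration.** All rates here are assumptions; only the 10 patients per arm comes from the plan (section 2.6).

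Proportion captured by the question = proportion with an unrecorded mild discomfort × probability that it is attributed to the product.

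- Assume 40% of every arm has such a discomfort.
- Placebo, attribution 25%: 0.40 × 0.25 = 0.10, or 1 of 10 patients.
- Active, attribution 25%: 0.40 × 0.25 = 0.10, or 1 of 10.
- Active, attribution 75%: 0.40 × 0.75 = 0.30, or 3 of 10.

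With no true difference, the question gives 10% against 10% to 30%. If attribution is equal the gap is zero, although the question still recovers only 10 of the 40 percentage points.

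**Step 4: dilution.** Suppose a further 40% of each arm has a symptom recorded in the diary, and the answers are pooled. Placebo becomes 0.40 + 0.10 = 0.50. Active becomes 0.50 to 0.70. The ratio is then 1.0 to 1.4, against 1.0 to 3.0 for the question alone. Section 2.8.8 does not say whether the answers to this question enter the between-arm comparison at all.

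**The case against.** The strongest reply is that this is an add-on. The quoted sentence says patients are *also* asked; the diary can hold mild and unrelated symptoms; and the usual gastrointestinal complaints are graded and asked about whatever their cause. All of that stands, and it rules out several stronger readings that a reader might infer.

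- *That visits ask only about product-related discomforts.* The diary is evaluated at every visit, and CTCAE grading has no such limit.
- *That a light symptom blamed on chemotherapy has nowhere to go.* The diary has a mild level and a no option for relationship. The most that can be said is that, if it is missing from the diary, this question does not ask for it.
- *That the same filter applies at withdrawal.* Section 2.2 says "they will be asked if their decision is related to any adverse event due to the consumption of the miraculin-based tablets". That is a question about the reason for leaving, not a means of collecting symptoms, and section 5 reports reasons other than adverse events.
- *That the whole tolerance comparison is biased, perhaps threefold.* A ratio of that order describes the add-on question alone, under assumed inputs.

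It can also be said that the sentence is only loosely written. It may mean discomforts left out of the diary because they seemed light, with the product link loosely attached, and the passive verb does not say who judges. Section 2.14 also gives the medical team the evaluation of adverse events. This is fair, but it does not answer the point: staff have to follow the sentence as written, and its plain reading makes relatedness a condition. The unfiltered diary is no remedy either, because the question exists to catch what the diary missed.

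Finally, differential attribution is not demonstrated. Section 5 reports that six of ten dropouts cited distorted taste of acidic foods, but the text does not give their arms.

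**Conclusion.** The point holds in a narrow form. For one of the routes in section 3.4.7, presumed relatedness decides what is collected. This is worse than the method the same section uses for the diary, where relatedness is recorded after the event. The possible consequence is differential ascertainment of mild, otherwise unrecorded symptoms, in a secondary outcome that section 2.8.8 compares between treatments.

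The size is unknown. The illustration of 1 against 1 to 3 patients of 10 per arm rests entirely on the assumed 40%, 25% and 75%, and the effect on the comparison disappears if attribution is equal across arms. That active-arm patients notice the taste change is plausible from the product's described action. That they attribute symptoms differently because of it is an inference, and the documents do not settle it. The correction is worth making because it is nearly free, not because a large bias has been shown.

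**What to change.** Reword the visit question. At every visit, ask all patients the same open question about any new or worse symptom since the last visit that is not in the diary, whatever its presumed cause. Record relatedness afterwards as a separate attribute, as the diary already does, and do not let it decide what is entered. State in section 2.8.8 that all-cause symptoms are compared between arms.

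The cost is one reworded question and a few more trivial chemotherapy-related entries, which should arise in all arms. Section 5 reports patients who have already completed the trial. For data already collected under the present wording, answers to this question should be kept apart from the diary and CTCAE data where their source can be identified.
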